## Introduction

Atrial fibrillation (AF) is characterized by beat-to-beat changes in the pattern of activation within the atria, unlike organized arrhythmias such as atrial flutter and atrial tachycardia. This chaotic nature poses a challenge with regard to understanding the pathophysiology and effective treatment of AF as shown by the frequent recurrences after AF therapy [1–4]. Due to the limited knowledge about the mechanisms involved, each AF patient is currently approached in the same manner. Based on the symptomatology and a clinical assessment the arrhythmia is either accepted or attempts are made to retain sinus rhythm with non-selective treatment modalities. However, this approach does not take account of the diversity among AF patients. AF occurs, for example, in association with mitral valve disease, hypertension, congenital heart disease, or cardiac surgery, or in young or older patients without any comorbidity (“lone AF”) [5, 6]. Furthermore, AF can have different clinical manifestations including paroxysmal, persistent, or longstanding persistent. On the structural level, the degree of fibrotic tissue in AF patients demonstrated heterogeneity as well and does not always predict the severity of the AF burden [7]. Therefore, it is likely that the pathophysiological mechanisms may differ between patients with AF. If these can be unraveled the possibility for targeted treatments may arise.

So far, several ablation procedures have been developed aiming to ablate a trigger site for initiation of AF or an arrhythmogenic substrate perpetuating AF. The isolation of triggers residing in the pulmonary veins demonstrated to be most successful in patients with paroxysmal AF. Nonetheless, recurrences occur frequently especially in patients with persistent AF, suggesting an incomplete eradication, reformation, or progression of the arrhythmogenic substrate. Other strategies include the ablation of rotors, ganglionated plexi, and complex fractionated electrograms [8–10]. However, these therapies have similar, limited success rates and there are no guidelines as to which strategy to choose for an individual patient.

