## Methods

### Study Population

All patients 18 years and older, with structural or coronary heart disease scheduled for elective cardiac surgery will be asked to participate. Patients who have a high-risk of complications during surgery or hemodynamic instability by inducing AF such as Wolff-Parkinson-White syndrome, poor left ventricular function (<40 %), presence of assist devices, hemodynamic instability, usage of inotropic agents, and kidney or liver failure are excluded from this study. Furthermore, patients with medical histories predisposing them for adhesions making epicardial mapping unfeasible or presence of an iatrogenically altered atrial electrophysiology such as prior radiation of the chest for malignancies, redo-cardiac surgery, paced atrial rhythms, and prior ablative therapy in the atria are excluded as well. Each patient, prior to enrolling in the study, will be provided with a written explanation of the study procedure together with an assessment of risks in participating in the study. Patients will be enrolled after the written informed consent form is signed. After enrollment patients are assigned to a group according to the underlying heart disease and whether their medical history includes AF. These groups consist of the following surgical procedures: coronary artery bypass grafting (CABG), mitral valve surgery, aortic valve surgery, mitral valve surgery with CABG, aortic valve surgery with CABG, and congenital heart surgery. Each of these groups are divided into separate groups for patients with and without prior AF episodes. Figure 1 demonstrates the inclusion and following procedures for patients participating in the study.

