**Fig. 1 Fig1:**
[figure not shown]
Flow-chart of patient inclusion and following study procedures. After enrollment, patients are assigned to 1 of 12 groups for data analysis according to the presence of previous atrial fibrillation (*AF*) occurrence and the type of surgery that will be performed (i.e., underlying heart disease). Subsequently, all patients are mapped during surgery and continuously monitored after surgery to detect postoperative AF. During the 5-year follow-up (*FU*), the additional tests consist of an electrocardiogram (*ECG*) and Holter monitoring when patients indicate symptoms suspected of AF. *ICF* informed consent form, *CABG* coronary artery bypass grafting, *MV* mitral valve surgery, *AV* aortic valve surgery, *CHD* congenital heart disease

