### Data and Statistical Analysis

Local activation times of the recorded atrial signals will be marked, from which color-coded activation and wave maps will be reconstructed by custom-made software which has previously been described in more detail [11]. Data exclusion criteria include progressive in- or decrease in AF cycle length (AFCL) between sequential recordings (recorded via the reference signal) indicated by an approximately two times in- or decrease in AFCL, recordings of other rhythms than sinus rhythm or AF, or ≥50 % of missing recording data. Data analysis and the criteria for data inclusion are demonstrated in Fig. 2. Electrophysiological parameters that will be derived include conduction velocity, incidence of conduction block, number of fibrillation waves, incidence of epicardial breakthroughs, AFCL, dominant frequency, electrogram voltage (the amplitude of the highest deflection in case of fractionation) and fractionation [11, 12]. For analysis, the electrodes of the mapping array are assigned to quadrants of 1 cm^2^. The variables will consist of averaged values or the percentage of occurrence/incidence for each quadrant. Figure 3 illustrates the construction of an activation map during sinus rhythm, quadrant partition, and its conversion into various parameters of all atrial sites. Figure 4 shows a wave map during AF and the variables that will be analyzed. Furthermore, rotor occurrence and the relation between patterns of activation, fractionation, fibrillation intervals, conduction abnormalities, and voltage will be studied and compared between the different atrial sites, atrial rhythms, and patient groups. Rotors will be defined as a wave of excitation rotating around a phase singularity for one or more cycles [15] and analyzed by determining the dominant frequencies at each recording site in order to identify high-to-low frequency gradients and determination of the degree of linking of fibrillation waves, indicative of repetitive patterns of activation. Linear regression analysis and paired Student’s *t* test will be used to compare various electrophysiological parameters between different sites and different atrial rhythms. Unpaired Student’s *t* test will be used to compare various electrophysiological parameters between patient groups.

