**Fig. 4 Fig4:**
[figure not shown]
*Left*: wave map during atrial fibrillation at the right atrial free wall. A total of 5 waves activate the recording area in 41 ms; 3 peripheral waves (*black arrows*) and 2 initiate at epicardial breakthroughs (*white star and white arrows*). *Black lines* between electrodes indicate conduction block (<18 cm/s). Isochrones of waves are set at steps of 5 ms after T_0_. Parameters derived from the wavemap include a number of epicardial breakthroughs, waves, and conduction velocity. *Right*: Examples of corresponding electrograms are shown. The parameters that will be derived from electrograms include atrial fibrillation cycle length (AFCL), fractionation, and voltage

The present study is the first that will explore the value of various parameters in discriminating the arrhythmogenic substrate of different patients with AF. We aim for a sample of (at least) 50 subjects in each group for the following reasons. First, our initiative should be considered as an exploratory study. We want to obtain early results in a relative limited number of patients, which will provide a basis for future (in depth) investigations. Therefore, we accept that our study will be underpowered to draw definite conclusions with good precision. Additionally, it is relevant to obtain estimates with sufficient precision, also in early, hypothesis generating studies such as ours. In the binomial distribution, a probability of an observation of 50 % is achieved with the greatest measurement error. Taking that probability as the ‘worst case’, in a dataset of 50 patients, the 95 % confidence intervals (CIs) around an observation would be ±14 %. In the 6*50 = 300 AF patients together, the 95 % CIs would be ±6 %. We consider these precisions acceptable for this exploratory study that will, hopefully, discover parameters that may be used in future studies to discriminate between AF patients with different underlying heart diseases.

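### The between-group test is the pooled-variance Student's t test, although group sizes may turn out unequal; Welch's form would protect the error rate at almost no cost

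*Protocol article*

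**What the plan says.** The section Data and Statistical Analysis assigns one method to each type of comparison. Linear regression and the paired t test serve contrasts between atrial sites and between rhythms. For contrasts between patient groups, the unpaired Student's "test will be used to compare various electrophysiological parameters between patient groups". The article mentions no check of variances and no unequal-variance form.

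Three other parts of the article bear on group size.

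- **Target.** The sample-size paragraph after the Fig. 4 legend says "We aim for a sample of (at least) 50 subjects in each group". This is a minimum, the same for every group, and no maximum is given.
- **How groups fill.** Under Study Population, "After enrollment patients are assigned to a group according to the underlying heart disease and whether their medical history includes AF". The Fig. 1 legend adds that "patients are assigned to 1 of 12 groups for data analysis". Group membership follows the patient's condition, so the design does not balance the numbers.
- **Loss of AF recordings.** Under Study Procedure, induction is abandoned if the top pacing rate fails or capture is lost. The Fig. 2 legend removes AF data after more than two reinductions. Data and Statistical Analysis also removes recordings with marked drift in AF cycle length or with half or more of the data missing.

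**The concern.** The pooled test estimates one common variance, weighted towards the larger group. If the smaller group is the more variable, the pooled standard error is too small: intervals are too short and false positives rise. If the larger group is the more variable, the standard error is too large and real differences are missed.

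The study will screen many electrophysiological parameters across up to 12 groups, to find those that discriminate between patients with different heart diseases. An error rate that moves with the size and spread of each pair would affect which parameters are carried forward. The point is separate from adjustment, multiplicity and the use of quadrants as units, because it remains with one value per patient.

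**Working it through.** **The plan's own figures.** The only precision figures are binomial half-widths at a proportion of 50%: "in a dataset of 50 patients, the 95 % confidence intervals (CIs) around an observation would be ±14" per cent, and "In the 6*50 = 300 AF patients together, the 95 % CIs would be ±6" per cent.

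- n = 50: 1.96 × √(0.25/50) = 0.139, which rounds to 14%.
- n = 300: 1.96 × √(0.25/300) = 0.057, which rounds to 6%.

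Both reproduce. Neither depends on the t test, so the present point does not touch them.

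**Inputs for the check.** The test and the floor of 50 come from the article. The larger sizes (100, 150) and the SD ratios (1.5, 2, 3) are assumptions, because the article gives no SD for any parameter and no unequal sizes.

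**Formulas.** For group sizes n1, n2 and standard deviations s1, s2:

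- pooled variance: sp² = [(n1 − 1)s1² + (n2 − 1)s2²] / (n1 + n2 − 2)
- pooled SE = √[sp²(1/n1 + 1/n2)]
- true SE = √(s1²/n1 + s2²/n2)
- approximate type I error = 2 × [1 − Φ(1.96 × pooled SE / true SE)]

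**50 v 50, SD 1 and 2.** sp² = (1 + 4)/2 = 2.5. Pooled SE = √(2.5 × 0.04) = 0.316. True SE = √(0.02 + 0.08) = 0.316. The ratio is 1, and with equal sizes it is 1 whatever the SDs.

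**100 (SD 1) v 50 (SD 2).** sp² = (99 + 49 × 4)/148 = 1.993. Pooled SE = √(1.993 × 0.03) = 0.245. True SE = √(0.01 + 0.08) = 0.300. Ratio 0.815, so type I error ≈ 2 × [1 − Φ(1.60)] = 11%.

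**100 (SD 2) v 50 (SD 1).** sp² = (99 × 4 + 49)/148 = 3.007. Pooled SE = √(3.007 × 0.03) = 0.300. True SE = √(0.04 + 0.02) = 0.245. Ratio 1.226, so type I error ≈ 2 × [1 − Φ(2.40)] = 1.6%.

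**Simulation.** Normal data, 100,000 data sets per setting, two-sided nominal 5%:

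| Sizes | SD ratio | More variable group | Pooled SE / true SE | Student | Welch |
|---|---|---|---|---|---|
| 50 v 50 | 1.5 | either | 1.000 | 4.9% | 4.8% |
| 50 v 50 | 2 | either | 1.000 | 5.1% | 5.0% |
| 50 v 50 | 3 | either | 1.000 | 5.1% | 5.0% |
| 100 v 50 | 1.5 | smaller | 0.878 | 8.5% | 5.0% |
| 100 v 50 | 1.5 | larger | 1.138 | 2.6% | 5.0% |
| 100 v 50 | 2 | smaller | 0.815 | 11.0% | 4.9% |
| 100 v 50 | 2 | larger | 1.226 | 1.7% | 5.0% |
| 150 v 50 | 1.5 | smaller | 0.822 | 10.7% | 4.9% |
| 150 v 50 | 1.5 | larger | 1.216 | 1.8% | 5.1% |
| 150 v 50 | 2 | smaller | 0.732 | 15.3% | 5.1% |
| 150 v 50 | 2 | larger | 1.364 | 0.8% | 5.1% |

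For confidence intervals the same figures mean that a nominal 95% pooled interval covers between 100 − 15.3 = 84.7% and 100 − 0.8 = 99.2% in these settings.

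**Cost of Welch when variances are equal.** With the effect set for about 80% power, Student and Welch give 79.3% and 79.3% at 50 v 50, 79.7% and 79.4% at 100 v 50, and 79.7% and 79.1% at 150 v 50. The loss is 0 to 0.6 percentage points.

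**The case against.** The strongest reply is that the defect needs two conditions, and the article states neither. It sets one target for all groups and multiplies it as 6 × 50, which describes equal groups. At that target Student's test holds its level even at an SD ratio of 3. This stands, and it makes the point conditional.

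A second reply is that a journal article may leave the variance option to a fuller document. This stands only in part. The article is not silent: it names Student's test, and the unequal-variance version goes by another name. If a fuller plan already uses Welch, only the label needs changing.

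Third, the study is exploratory and says it will be underpowered for definite conclusions. That lowers the severity. It does not make a less robust test preferable when the robust one costs almost nothing.

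Several stronger readings are tempting but unsupported:

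- **That reported results are already wrong.** The article contains no p-value or interval from a t test.
- **That the groups with prior AF must be more variable.** A reader might infer this from the Introduction's remark that "this approach does not take account of the diversity among AF patients". That sentence says AF patients differ from one another. It does not compare their spread with that of patients without AF.
- **That counts and percentages inflate the type I error because variance rises with the mean.** If two groups have the same mean, that mechanism gives them the same variance. It can affect intervals where means truly differ, but it does not produce the error rates above.
- **That regression also needs robust standard errors.** The planned regression concerns sites and rhythms, not group contrasts.

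**Conclusion.** The point holds in conditional form and is minor. The article fixes a pooled-variance test for group contrasts in a design where analysed sizes can realistically differ: 50 is a floor, patients fall into groups by diagnosis and history, and AF recordings can be lost. If spread differs as well, the test and its intervals can err in either direction. The range is about 8 to 15%, or about 1 to 3%, against a nominal 5%, depending on whether the smaller or the larger group is the more variable. It rests on assumed sizes of 50 v 100 to 150, assumed SD ratios of 1.5 to 2, and normal data with one value per patient. The actual imbalance and spread cannot be computed from the article, and at exactly 50 v 50 there is no problem of level.

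**What to change.** In Data and Statistical Analysis, replace the unpaired Student's t test with Welch's t test, reported with its confidence interval, for comparisons between patient groups. Specify it outright, without a preliminary test of variances. The paired t test and the regression for sites and rhythms need no change on this account.

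The cost is a change of test name, with no new data and no change in sample size. When variances are in fact equal, the power loss is under 1 percentage point.

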**Fig. 2 Fig2:**
[figure not shown]
Flow-chart of data evaluation. Atrial fibrillation (*AF*) data from patients that were reinduced >2 times is excluded. Custom-made software detects atrial markings with the presented properties for sinus rhythm (*SR*) and AF. If ≥50 % of a 1 cm^2^ quadrant is not marked, this quadrant will be excluded from further analysis. Rhythm evaluation is performed with use of the activation and wave maps, and the position in SR is evaluated for overlap with a total SR map constructed with use of the reference signal. All data is manually checked, from which the parameters are derived afterwards

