### Study Procedure

Epicardial mapping is performed during open heart surgery [13]. Patients will be under general anesthesia and vital signs will be monitored continuously throughout the procedure. Mapping will be performed before going on extracorporeal circulation, during sinus rhythm, and (induced) AF. AF is induced by fixed rate pacing at the right atrial appendage with a pulse width of 2 ms delivered by temporary pacemaker wires. Pacing bursts will start at a rate of 250 bpm and will be increased with steps of 50 bpm each time AF is not induced after 3 attempts. If AF is not induced at a pacing rate of 400 bpm or loss of capture occurs, attempts will be terminated. As AF is induced it may terminate spontaneously, otherwise, if an induced arrhythmia sustains after the mapping procedure, electrical cardioversion will be performed immediately afterwards. If a patient is in AF at the onset of the mapping procedure, mapping will be performed during AF and during sinus rhythm after electrical cardioversion if there is no atrial thrombus present on transesophageal echocardiogram.

Epicardial mapping of the right and left atria will be performed using a custom-made electrode array (192 electrodes, diameter 0.45 mm, 2-mm inter-electrode distance; GS Swiss, Küssnacht, Swiss). All electrograms recorded by the electrode are stored on hard disk after amplification (gain 1000), filtering (bandwidth 0.5–400 Hz), sampling (1 KHz) and analogue to digital conversion (16 bits). An indifferent electrode is attached to a steal wire fixed in subcutaneous tissue and a reference signal is attached to the right atrium. In addition, a ventricular surface electrocardiogram (ECG) is recorded simultaneously. Signals will be recorded at 9 right and left atrial sites during sinus rhythm for 5 s per site and during (induced) AF for 10 s per site. Mapping is initiated at the lower right atrium and is proceeded upwards over the right atrial appendage. Thereafter, the left atrium will be mapped starting between the pulmonary veins and will continue along the atrioventricular groove from the lower pulmonary veins to the left atrial appendage and finally at the roof of the left atrium for Bachmann’s bundle. The mapping positions are demonstrated on a 3D model in the online Supplementary Video (1). The entire mapping procedure will not prolong the surgical procedure by more than 10–15 min [13].

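### The reinduction rule lets one patient's AF sites come from up to three episodes, and the stated site comparisons and frequency gradients have no episode term

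*Protocol article*

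**What the plan says.** **Retention rule.** The Fig. 2 caption states that AF "data from patients that were reinduced >2 times is excluded". AF data with no, one or two reinductions are kept.

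**Recording.** Under Study Procedure, "Signals will be recorded at 9 right and left atrial sites", and "during (induced) AF for 10 s per site". The order is fixed: "Mapping is initiated at the lower right atrium and is proceeded upwards over the right atrial appendage". The left atrium follows, and Bachmann's bundle comes last. The same section foresees that an induced episode may not last: "As AF is induced it may terminate spontaneously".

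**Analysis.** Under Data and Statistical Analysis, linear regression and the paired t test "will be used to compare various electrophysiological parameters between different sites and different atrial rhythms". The rotor analysis includes "determining the dominant frequencies at each recording site in order to identify high-to-low frequency gradients". No term for AF episode is named.

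**Existing guard.** The same section excludes data when AFCL on the reference signal changes progressively between successive recordings, by a factor of about two. Study Limitations acknowledges that recording is sequential.

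**The concern.** Each induction starts a new AF episode. If the first stops partway through the sequence and mapping continues in a second, the difference between an early and a late site contains both a site effect and an episode effect. Because the order always runs from right to left, the two are confounded in the same direction in every such patient.

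Two outputs are exposed. The first is the individual map, where a frequency gradient is part of the planned rotor analysis and feeds the study's aim of locating each patient's substrate. The second is the group-level paired site comparison, whose mean could shift if AFCL tends to be shorter or longer after reinduction. A progressive-drift rule is not built for a step between episodes.

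**Working it through.** **The plan's own figure.** The article gives no figure on this point. Its only precision statement reproduces: 1.96 × √(0.25/50) = 0.139 (stated ±14 %) and 1.96 × √(0.25/300) = 0.057 (stated ±6 %). The point does not rest on these; they supply only the sample sizes 50 and 300 used below.

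**Episodes per patient.** One initial induction + at most 2 retained reinductions = 3 episodes.

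**Time needed in one episode.** 9 sites × 10 s = 90 s of recording, plus the time to move the array.

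**Individual map (assumed inputs).** Take a within-patient between-episode SD of 10 to 20 ms, a mean AFCL of 200 ms and no true gradient. For two sites from different episodes, E|d| = √2 × SD × √(2/π) = 1.128 × SD:
- SD 10 ms: 11.3 ms
- SD 20 ms: 22.6 ms

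Near 200 ms, 1 ms corresponds to 1000/200² = 0.025 Hz, so these are about 0.28 and 0.56 Hz.

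**What the two-fold rule catches.** At 200 ms it needs a change to about 100 or 400 ms. With SD 20 ms, the difference between two episodes has SD √2 × 20 = 28.3 ms, so even the 100 ms drop is about 3.5 SDs. In the simulation below, a two-fold filter on the site pair removed at most about 0.6 % of pairs.

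**Group-level paired test (simulation, assumed inputs).** Last-mapped minus first-mapped site, no true site difference, mean AFCL 180 ms, between-episode SD 20 ms, site noise SD 10 ms, and one or two reinductions equally likely among those reinduced. Every reinduced patient has the first site in the first episode and the last site in the last one, which is the most exposed case. Expected false mean difference = share × 1.5 × shift; for example 0.25 × 1.5 × (−10) = −3.75 ms, against −3.7 ms simulated.

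| Share reinduced | Shift per reinduction | False mean difference | Rejections, n = 50 | Rejections, n = 300 |
|---|---|---|---|---|
| 10 % | 0 ms | 0.0 ms | 5 % | 5 % |
| 10 % | −10 ms | −1.5 ms | 8 % | 31 % |
| 10 % | −20 ms | −2.9 ms | 16 % | 75 % |
| 25 % | 0 ms | 0.0 ms | 5 % | 5 % |
| 25 % | −10 ms | −3.7 ms | 21 % | 85 % |
| 25 % | −20 ms | −7.1 ms | 56 % | 100 % |
| 50 % | 0 ms | −0.1 ms | 4 % | 4 % |
| 50 % | −10 ms | −7.5 ms | 52 % | 100 % |
| 50 % | −20 ms | −14.4 ms | 95 % | 100 % |

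With no systematic shift the test keeps its nominal 5 % level. With one, the error grows with the share reinduced and with sample size.

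**The case against.** **The article does not say that episodes are joined.** It does not describe how recordings from different episodes are combined or labelled, the Fig. 2 flow-chart is not shown, and the only total map it mentions is for sinus rhythm. A reader might infer that reinduced patients' recordings are merged into one nine-site map, with the first episode supplying the right atrium and later ones the left. The text supports neither: it does not say when AF stops, or whether mapping resumes or restarts after reinduction. AF may also end before the first site is recorded. This objection stands; what remains is that the rule permits the mixing.

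**Random differences do not bias the stated test.** This also stands, as the zero-shift rows show.

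**The bias between groups is unproven.** A reader might infer that the prior-AF versus no-prior-AF contrast is biased by a known amount. Suppose 40 % of no-prior-AF maps and 0 to 10 % of prior-AF maps mix episodes, with a true gradient SD of 10 ms. The mean absolute gradient is then 0.6 × 8.0 + 0.4 × 13.8 = 10.3 ms (between-episode SD 10) to 0.6 × 8.0 + 0.4 × 23.9 = 14.4 ms (SD 20), against 8.0 to 0.9 × 8.0 + 0.1 × 23.9 = 9.6 ms. The arithmetic is right, but the article never names that statistic and every input is assumed. Groups are defined by AF history, so prior-AF patients in sinus rhythm at surgery are induced too.

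**Rotors do not rest on a gradient alone.** They are defined by rotation around a phase singularity, and frequency gradients are paired with linking of waves. Linking measured within one recording is unaffected by a change of episode between recordings.

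**Controls exist, the study is exploratory, and the article is condensed.** The reference signal on the right atrium tracks AFCL independently of array position, the number of reinductions is capped, and all data are checked manually. These help, but none separates site from episode in the stated comparisons. An exploratory aim accepts imprecision; it does not remove a confounder. The point does not rest on omitted detail: the stated retention rule and the stated site comparisons together allow the mixing.

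**Conclusion.** The point holds in limited form. Retained AF data can span up to three episodes per patient. With a fixed site order, later-mapped sites, mostly left atrium and Bachmann's bundle, can come from later episodes when AF terminates during mapping. The stated comparisons cannot tell site from episode in those patients, and the two-fold AFCL rule would rarely intervene.

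In a single patient's map, either random or systematic episode differences can look like a gradient. In the group-level signed paired test, random differences cost precision only; a false mean site difference arises only if AFCL shifts systematically with reinduction. Such a shift is plausible, since mapping starts straight after induction and the article treats AFCL change during recording as a known problem, but the article does not establish it or its direction.

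All magnitudes above are illustrations. The article gives neither the share of reinduced patients nor the between-episode variation, so a bias between prior-AF and no-prior-AF groups is possible but cannot be quantified. Sinus-rhythm maps are not affected, nor is AF already present at the start of mapping and mapped without reinduction. This is an inexpensive improvement to the analysis, not a demonstrated error in results.

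**What to change.** Keep the inclusion rule and change only the analysis:

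- Tag every AF recording with its episode number. The reinduction count is already needed for the Fig. 2 rule.
- Compute AFCL gradients, dominant-frequency gradients and site comparisons only between sites recorded in the same episode. Alternatively, fit site effects with random effects for patient and for episode within patient.
- Add a sensitivity analysis restricted to single-episode patients. It matters most alongside the mixed model, because a systematic shift with reinduction is not a mean-zero random effect.
- Report per group how many patients contribute more than one episode.
- Keep all recordings for single-site parameters, including linking measured within one recording.

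The cost is analysis wording and code. Reinduced patients lose cross-episode site pairs, so intervals for right-to-left contrasts widen slightly. The single-episode analysis also favours patients whose induced AF lasted, so it should stay a sensitivity analysis. Inclusion was under way when the article was written, so episode tags for patients already mapped may have to be reconstructed from the stored recordings.
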